### What information is collected

Figure 2 provides a brief overview of the information collected from participating patients at the baseline and follow-up visits, including the minimum required data, which are assessed for all patients in all participating centres and additional data from tests performed in few centres and which will be collected if available for subgroup analysis to address additional research questions. Small exemptions are allowed when a minimally required examination was not performed due to, for example, the patient’s very young age, as long as each patient undergoes a specialised ENT examination at least once a year.

**Figure 2 F2:**
[figure not shown]
Overview of the information collected during the EPIC-PCD cohort study. ENT, ear–nose–throat; EPIC-PCD, ear–nose–throat prospective international cohort of patients with primary ciliary dyskinesia; SNOT-22, Sino-Nasal Outcome Test-22.

#### ENT examinations

The ENT examinations performed in the participating centres in addition to physical examination include nasal endoscopy (either rigid or flexible), nasal function tests (eg, patency and olfaction) tests, tympanometry, audiometry and auditory brainstem evoked response. Nasal endoscopy, tympanometry and audiometry are performed regularly at all centres during follow-up and belong to the minimum requirements for participation to the study; the remaining tests are performed only in selected, specialised centres either at initial diagnosis or during follow-up. When clinically indicated, patients will undergo CT of the sinuses or the ears. When available, we will collect data of previous imaging examinations of the sinuses or the ears from clinical records.

The data collected during the ENT examinations are predefined based on the ENT examinations module of the FOLLOW-PCD standardised form.^31^ Nasal endoscopy data include the presence and consistency of nasal discharge (eg, serous and mucopurulent), evaluation of nasal mucosa (eg, presence of erythema or oedema), visual evaluation of nasal polyps using the Lildholdt score,^38^ evaluation of hypertrophy or atrophy of nasal turbinates and description of septum and any deformities caused due to chronic infection. Otoscopy data include the presence and consistency of ear discharge, visual description of the tympanic membrane (eg, tympanic perforation, retracted membrane and tympanic sclerosis) and the presence of acute otitis media or OME. Results of tympanometry are recorded using the description of tympanogram type by Jerger and of audiometry using the type of audiometry and the WHO hearing loss grades.^39^ In addition, we record the presence of grommets or use of hearing aids. When sinus imaging is performed, we record the following findings: the presence of aplasia, hypoplasia, thickening of the bone and Lund-Mackay score.^40^

#### Other data from clinical records

At recruitment, baseline medical information and results of diagnostic tests will be extracted from clinical records and recorded using FOLLOW-PCD. In addition to the medical data from the upper airways, we collect data from lung function measurements, including spirometry and when available multiple breath-washout measurements and lung imaging. This information will allow us to assess associations between upper and lower respiratory disease in PCD.

On indication, nasopharyngeal or nasal swab samples, and when possible middle meatal samples, and sputum or cough samples for microbiological cultures and results will be collected. In case of otorrhoea, ear drainage samples will also be taken. We record the type of sample, the isolated pathogens and antibiotic resistance. We also collect information related to hospitalisations and surgical procedures related to upper airways disease and data on upper airway management.

#### Information from questionnaires

Participating patients are asked to complete the FOLLOW-PCD questionnaire at every visit and the QoL-PCD questionnaire at least once a year, as described earlier. The FOLLOW-PCD questionnaire includes sections on upper and lower respiratory symptoms, health-related behaviours (eg, exercise and smoking) and environmental factors. The QoL-PCD questionnaire assesses how the disease affects the QoL of patients with PCD.

### Study database

All collected data are entered into a secure web-based database using the database programme, Research Electronic Data Capture (REDCap) hosted by the Clinical Trials Unit, Bern.^41^ REDCap is widely used in academic research and allows data entry and extraction in various formats. Contributing centres are responsible for the pseudonymisation of the data contributed to the study. Only limited research staff from the EPIC-PCD data team has access to the whole dataset; local investigators at the EPIC-PCD clinics have access only to data from their clinic (box 1). Data generation, transmission, storage and analysis of health-related personal data within the study follow the Swiss legal requirements for data protection. All study team members are trained on data protection and dealing with particularly sensitive data.

Box 1Contributing to and accessing data in the EPIC-PCDHow to contribute dataCentres that wish to participate in the project and contribute data can contact the EPIC-PCD data team. As soon as ethical approval is obtained and centre representatives have signed a data delivery agreement, they will receive a password to access the online software REDCap and they will be able to enter their data directly prospectively. We offer information and technical support wherever needed.How to access dataParticipating centres keep constant access to their datasets and can export them directly in various formats for local analyses. Participating centres may also extract their datasets and contribute relevant data to other multinational projects or to the international PCD registry.The use of EPIC-PCD data from several centres for studies and publications is regulated by the EPIC-PCD committee, which consists of members of the EPIC-PCD data centre and representatives of the EPIC-PCD clinics. A series of publications are originally planned to be led by the EPIC-PCD data team, as part of the research grant funding the set-up and management of the study.For additional publications, collaborators should submit a concept sheet describing the planned analysis and publication to the committee, which will approve or oppose the planned publication and use of data. If the planned analysis is approved, a publication agreement will be signed and the EPIC-PCD data centre will prepare a partial dataset for the proposed analysis and will work closely with the lead researchers of each planned study for methodological input and support.For further details, contact: [contact], ear–nose–throat prospective international cohort of patients with PCD; REDCap, Research Electronic Data Capture.

#### Study power and sample size

We expect to recruit at least 450–550 patients in EPIC-PCD. This number is based on the study feasibility and the number of patients followed-up in the EPIC-PCD clinics and is considered large enough for a prospective study in such a rare disease and much larger than any other available PCD dataset on ENT disease. After the establishment of the cohort, it is now possible for more centres to join and contribute patients, resulting in even higher numbers of patients. The planned analyses are up to a point exploratory and do not follow specific hypotheses, although we have few assumptions based on the limited literature. This does not allow for a precise power calculation; however, we will ensure that each performed analysis has sufficient power to draw meaningful conclusions.

### Planned analysis and outcomes of interest

First, we will describe prevalence and severity of ENT problems, stratified by age, age at diagnosis, sex, country, ciliary ultrastructural defect or genetic mutation. Outcomes of interest will be sinonasal and otologic symptoms and signs (eg, rhinitis, loss of smell, sinusitis, otitis and impaired hearing) and the results of ENT examinations (mainly of nasal endoscopy, tympanometry, audiometry and when available imaging and SNOT-22). We will estimate prevalence of binary outcomes and mean values of continuous outcomes by using constant-only models. We will use logistic regression models for binary outcomes, and linear models for continuous outcomes. Associations with determinants will be assessed in multivariable mixed models.

As a second step, we will assess the association of baseline ENT problems with lung disease progression expressed in terms of lung function tests, sputum cultures and, if available, lung imaging results. For this analysis, lung function will be the main outcome, measured primarily with spirometry and plethysmography measuring forced expiratory vital capacity and forced expiratory volume in 1 s. Data will be converted into z-scores adjusted for sex, height, age and ethnicity, using the Global Lung Initiative reference values. In some centres, PCD patients also perform multiple breath washout measurements at follow-up, which have been reported to be more sensitive in detecting early lung disease. In those patients, Lung Clearance Index will be considered as a secondary outcome, if patients’ numbers allow it. We will use mixed models, including the baseline ENT disease characteristics with an interaction of each with age as fixed effects, and the patients and the centres as random effects.

Finally, we will analyse follow-up data on ENT symptoms and examinations to describe the short-term course of sinonasal and otologic disease during a 2-year follow-up, and identify determinants of disease prognosis. Here, outcomes of interest will be the severity of CRS (based on a symptoms score), loss of smell, bacterial colonisation of the upper respiratory tract, need of surgical management of the sinuses, recurrent otitis media, OME, hearing impairment and need of surgical management of the ears. We will first describe how the outcomes change over the follow-up time in binomial or multinomial (for outcomes with more than three categories, such as hearing impairment) mixed models, using separate models for each outcome. Then, we will study determinants of disease prognosis categorising patients in four groups for each outcome based on the evaluation at baseline and at 2-year follow-up: (a) patients who never reported the outcome, (b) patients negative for the outcome at baseline but positive at follow-up, (c) patients positive at baseline but negative at follow-up and (d) patients positive at both time points. We will use mixed-effects multinomial regression models, including all possible determinants as fixed effects. We will select possible determinants from characteristics available at baseline, including symptoms and measurements; age at diagnosis, ultrastructural defects and genetic mutations; and general patient characteristics, such as age and sex. We will make our determinants selection based on directed acyclic graphs, considering existing literature. Data will be collected prospectively and in a standardised way resulting in small data heterogeneity between participating centres; however, we will still need to account for possible differences between countries in all analyses. Thus, we will analyse all outcomes of interest using random-effects models that account for clustering of patients within participating centres.

For all analyses, results will be interpreted with caution considering the clinical importance and not just mere statistically significant findings. If needed, we will correct for multiple testing. All missing values will be described in detail; however, we expect this will not be an issue for the important variables as the data are collected prospectively. In case we have significant amount of missing data, we will consider subgroup analyses or multiple imputation of missing data to deal with this issue, depending on what is the most appropriate approach for the specific question and analysis.

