### Study objectives

This study aims to characterise ENT disease in patients with PCD and its association with lung disease, and to identify determinants of its course and prognosis. Specifically, we aim to: (a) assess the prevalence and severity of sinonasal and otologic symptoms and the frequency and range of signs and physiological findings assessed during standardised ENT physical examination, and describe possible differences by age; (b) study the association of sinonasal and otologic disease with lung disease in patients with PCD and (c) identify determinants of the course and prognosis of sinonasal and otologic disease in patients with PCD.

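### Binary prevalences: constant-only logistic models combined with the random-effects rule for all outcomes point to a zero-effect-centre probability, not the cohort prevalence; the article should say which is reported

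*Protocol article*

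**What the plan says.** Under *Study objectives*, aim (a) of the protocol article is to "assess the prevalence and severity of sinonasal and otologic symptoms", together with the frequency of examination findings and differences by age.

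Three statements under *Planned analysis and outcomes of interest* bear on how a prevalence is obtained:

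- The estimator: "We will estimate prevalence of binary outcomes and mean values of continuous outcomes by using constant-only models".
- The model family: "We will use logistic regression models for binary outcomes, and linear models for continuous outcomes". The next sentence brings in mixed models for a different purpose: "Associations with determinants will be assessed in multivariable mixed models".
- A general rule at the end of the analysis description: "we will analyse all outcomes of interest using random-effects models that account for clustering of patients within participating centres".

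The first step uses the term outcomes of interest for the ENT symptoms, signs and test results, so the general rule covers them. A patient-level random effect is named once, in the lung-function model of the second step, which takes "the patients and the centres as random effects". The article does not say how a percentage is obtained from a fitted constant-only model.

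**The concern.** In a linear random-intercept model the constant is a mean, so one sentence can serve for continuous outcomes. In a logistic random-intercept model the constant is the log-odds in a centre whose random effect is zero. Because the logit link is non-linear, its back-transform is not the average probability over centres. It is pushed away from 50%: uncommon findings look rarer and common ones commoner.

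The size of the shift depends on the between-centre variance, so it can differ between outcomes and strata. The article stratifies by country, and its centre list has 11 centres in nine countries, with two each in France and Turkey and one in each of the other seven. In a single-centre country no centre effect can be separated from the constant, so the country figure is in effect the crude proportion, while the overall figure would refer to a zero-effect centre. The two would not be on the same footing.

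At stake is the first thing the study sets out to report. The shift is systematic, so recruiting more patients would not remove it.

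**Working it through.** **Inputs.** From the article: 11 centres (*Inclusion criteria and participating centres*) and at least 450 to 550 patients (*Study power and sample size*). It states no prevalence, between-centre SD or intraclass correlation, so it has no figure to reproduce. Assumed here: a normal centre effect on the logit scale with SD s from 0.25 to 1.5, and illustrative prevalences of 10%, 20%, 50% and 80%.

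**Formula.** For cohort prevalence p, solve p = E[expit(b + sZ)] for b, with Z standard normal (80-point Gauss-Hermite quadrature), and report expit(b), the back-transformed constant. The latent-scale intraclass correlation is s² / (s² + π²/3); for s = 1.0 this is 1 / (1 + 3.29) = 0.23.

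| Assumed centre SD (ICC) | True 10% | True 20% | True 50% | True 80% |
|---|---|---|---|---|
| 0.25 (0.02) | 9.8% | 19.7% | 50.0% | 80.3% |
| 0.5 (0.07) | 9.2% | 18.9% | 50.0% | 81.1% |
| 0.75 (0.15) | 8.2% | 17.6% | 50.0% | 82.4% |
| 1.0 (0.23) | 7.1% | 16.1% | 50.0% | 83.9% |
| 1.5 (0.41) | 5.0% | 12.8% | 50.0% | 87.2% |

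For a true 20% the gaps are 0.3, 1.1, 2.4, 3.9 and 7.2 points going down the table.

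**Scale for comparison.** The simple binomial 95% half-width is 1.96 × √(p(1 − p)/n). At p = 20%, 1.96 × √(0.20 × 0.80 / 450) = 3.7 points, and 3.3 points at n = 550. At p = 10% it is 2.8 and 2.5 points. The gap therefore exceeds this half-width at SD 1.0 (3.9 points at 20%, 2.9 at 10%) and is well inside it at SD 0.5 or less. The half-width ignores clustering and so understates the real uncertainty, which makes the comparison generous to the concern.

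**Check by simulation.** 11 centres of 45 patients (495 in total; equal size is an assumption), 400 cohorts per scenario, random-intercept logistic model fitted by maximum likelihood. Means over the cohorts:

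| True prevalence, centre SD | Crude | Back-transformed constant | Averaged over fitted centre effects |
|---|---|---|---|
| 20%, 0.5 | 19.9% | 19.0% | 19.9% |
| 10%, 1.0 | 9.8% | 7.2% | 9.8% |
| 20%, 1.0 | 19.8% | 16.3% | 19.7% |
| 80%, 1.0 | 79.9% | 83.5% | 80.0% |

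Averaging the same fitted model over its centre distribution recovers the cohort figure.

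**The other reading.** Without random effects, the score equation of a constant-only logistic model is Σ(y − p) = 0, so the estimate is exactly the crude proportion. The point estimate is then right, but the model does not follow the general rule, and its standard error treats patients from one centre as independent.

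**The case against.** The strongest reply is that the article never states the faulty step. It says prevalences are estimated by means of constant-only models, not that the constant is back-transformed with the random effect set to zero. Averaging over centres is a routine step after fitting, and a condensed article may leave it to a fuller document. Within the first step, moreover, mixed models are named only for associations, so the prevalence sentence alone describes a plain logistic model that returns the crude proportion. This stands in part: the wrong quantity is a risk created by combining two sentences, not a declared choice. It does not remove the point, because the rule for all outcomes contradicts the plain-model reading.

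A second reply is that the article expects little heterogeneity between centres. If so, the gap is about a point or less. That expectation rests on standardised data collection, however, and not on case mix. The cohort takes all ages, two listed centres are named children's hospitals, and the introduction describes ear disease easing and sinonasal disease possibly worsening with age. Larger centre differences are possible, though the article does not quantify them.

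A reader might also infer more than the text supports:

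- *That the constant describes a median patient, or that the follow-up analysis misstates prevalence or its change.* The follow-up models describe change over time and are not constant-only. No patient effect is named for them, and they are not said to supply a prevalence. A conditional odds ratio is a legitimate quantity unless it is presented as a population one.
- *That every binary outcome is biased.* The gap is zero at 50% and negligible when the centre variance is small.
- *That means of continuous outcomes are affected.* The linear model has no such link problem; only the weighting of centres differs.

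Finally, aim (a) does not say whether patients or centres are to be weighted equally. That is fair, and is a reason to state the target.

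**Conclusion.** The point holds as a conflict to be reconciled for the binary outcomes of the first step. Applied together, the two sentences lead naturally to a zero-effect-centre probability; applied separately, they contradict each other and the interval ignores clustering. On neither reading does the text deliver a cohort prevalence with a valid interval unless a step is added.

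The size is conditional on an assumed between-centre SD and a normal centre effect: about 1 point or less at SD 0.25 to 0.5, about 3 to 4 points at SD 1.0 for prevalences of 10%, 20% or 80%, and nothing at 50%. If heterogeneity is as small as the article expects, the practical effect is minor. The documents do not show that the reported prevalences will in fact be wrong, and the point does not extend to the follow-up models or to continuous outcomes.

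**What to change.** In the first step of *Planned analysis and outcomes of interest*, state that overall and stratum prevalences of binary outcomes are patient-weighted population-averaged proportions. Obtain them from an ordinary logistic or independence GEE model, with centre-clustered intervals and a small-sample correction for 11 centres. A clustered interval cannot be computed within a single-centre country, so name a simple binomial interval there.

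An acceptable alternative is to keep the random-intercept model and average its fitted probabilities over the estimated centre distribution. The text should then note that this weights centres differently from the crude proportion, and that the two can differ if centre size is related to prevalence.

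Reword the closing rule so that random-effects models apply to associations and determinants, with the prevalence estimates as a named exception that handles clustering through the interval. Keep the mixed models for associations.

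The cost is a few sentences and one analysis step, with no new data. The small downside is that the intervals need a small-sample correction under the first option, or the delta method or a bootstrap under the second.

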## Methods and analysis

### Study design

The ENT prospective international cohort of patients with PCD (EPIC-PCD) is a prospective observational clinical cohort set up as a multinational multicentre study. It is embedded into routine patient care of participating reference centres for PCD and patients continue to be managed according to local procedures and protocols. The study is hosted at the Institute of Social and Preventive Medicine (EPIC-PCD data centre) at the University of Bern, Switzerland, and is managed in collaboration with participating centres (EPIC-PCD clinics).

Patient data are collected prospectively. Baseline information is collected at the enrolment of the patient in the study and follow-up data during clinical follow-up visits at the participating centres. The study has no foreseen endpoint. Patient follow-up is planned for a minimum period of 4 years; however, it will be extended if collaborators agree.

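### The four-group multinomial model mixes prevalence at entry with prognosis, and group (a) is worded inconsistently with the two-time-point grouping

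*Protocol article*

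**What the plan says.** The last analysis under Planned analysis and outcomes of interest is meant to describe the short-term course of sinonasal and otologic disease and to "identify determinants of disease prognosis". Mixed models first describe change over follow-up. The determinants step then proceeds by "categorising patients in four groups for each outcome based on the evaluation at baseline and at 2-year follow-up". The first two groups are "patients who never reported the outcome, (b) patients negative for the outcome at baseline but positive at follow-up"; the other two are given as "c) patients positive at baseline but negative at follow-up and (d) patients positive at both time points".

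On the model, the article states: "We will use mixed-effects multinomial regression models, including all possible determinants as fixed effects". On the candidates, it states: "We will select possible determinants from characteristics available at baseline, including symptoms and measurements". Selection is to be guided by directed acyclic graphs, and centres enter as random effects. The section names no reference group, no contrast within baseline status and no conditioning on baseline status.

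Clinic visits take place every 3 to 6 months (Clinical assessments), with a detailed ENT examination at least yearly. Under Information from questionnaires: "Participating patients are asked to complete the FOLLOW-PCD questionnaire at every visit".

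**The concern.** The four groups cross two things: whether the patient had the outcome at entry, and what happened afterwards. Groups (a) and (b) start negative; (c) and (d) start positive. A coefficient that compares a group from the first pair with one from the second therefore reflects who already had the problem at enrolment as well as how it developed. Only (b) vs (a), which is onset, and (d) vs (c), which is persistence, concern course alone. Objective (c) of the study is to identify determinants of course and prognosis, and this is the only determinants-of-prognosis analysis that the article describes. If the full coefficient set, or a joint test over the four groups, is reported as prognosis, correlates of prevalence at entry can be presented as prognostic factors.

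The candidate list makes this more likely. Baseline symptoms and measurements are eligible, and the baseline status of the outcome itself defines the groups. If that status entered as a determinant, it would separate (a) and (b) from (c) and (d) by construction.

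A smaller problem is the wording of group (a). The other three groups are set by two evaluations, whereas (a) asks that the outcome was never reported.

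**Working it through.** The article gives no derived figure on this point and no prevalence, onset or persistence rates, so there is nothing to reproduce. The rates below are assumptions. Only the 450 to 550 patients (Study power and sample size) and the visit interval come from the document.

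**1. Which contrasts cross baseline status.** With (a) as reference, the coefficients are b/a (within), c/a and d/a (across). With (b): a/b within, c/b and d/b across. With (c): d/c within, a/c and b/c across. With (d): c/d within, a/d and b/d across. Two of three cross baseline status in every case.

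**2. What the crossing contrasts estimate.** Let p be baseline prevalence, i the onset risk among baseline-negatives and s the persistence risk among baseline-positives. Then

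- P(a) = (1−p)(1−i), P(b) = (1−p)i
- P(c) = p(1−s), P(d) = p·s

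For a binary factor with levels 0 and 1, the relative-risk ratio (RRR) for (d) vs (a) is

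RRR = [p1/(1−p1)]/[p0/(1−p0)] × s1/s0 × (1−i0)/(1−i1).

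The first term is the baseline odds ratio. For (c) vs (a), s is replaced by 1−s. If i and s are the same in both levels, both RRRs reduce to the baseline odds ratio, whatever i and s are. The RRRs for (b) vs (a) and (d) vs (c) contain no p and equal 1.

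**3. Numbers.** Assume i = 15%, s = 70%, and prevalence 30% vs 40%.

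- Level 0: (a) 0.595, (b) 0.105, (c) 0.090, (d) 0.210
- Level 1: (a) 0.510, (b) 0.090, (c) 0.120, (d) 0.280
- (c) vs (a): (0.120/0.510)/(0.090/0.595) = 1.56
- (d) vs (a): (0.280/0.510)/(0.210/0.595) = 1.56
- (b) vs (a): (0.090/0.510)/(0.105/0.595) = 1.00
- (d) vs (c): (0.280/0.120)/(0.210/0.090) = 1.00

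For 30% vs 60% the crossing RRRs are (0.6/0.4)/(0.3/0.7) = 3.50, and for 50% vs 70% they are (0.7/0.3)/(0.5/0.5) = 2.33. The within-status RRRs stay at 1.00.

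**4. How often such a factor would be flagged.** Simulation with 3,000 runs per setting, i = 15%, s = 70%, factor levels of equal size, two-sided 5% level, independent patients and no centre effect. The factor has no effect on course. Where two figures stand, they are for N = 450 and N = 550.

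| Baseline prevalence | Four-group test, 3 df | (d) vs (a) | Within baseline status, 2 df |
|---|---|---|---|
| 30% vs 40% | 43%, 54% | 48%, 57% | 4.6%, 5.1% |
| 30% vs 45% | 81%, 89% | 81%, 88% | 5.9%, 5.7% |
| 30% vs 60% | 100%, 100% | 100%, 100% | 5.7%, 4.6% |

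The Monte Carlo standard error at 5% is √(0.05 × 0.95/3000), about 0.4 percentage points, so the within-status test stays close to its nominal level.

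**5. Group (a).** If (a) means negative at both evaluations, the groups form the complete 2×2 table for everyone with both evaluations. Read literally, a patient negative at both but positive in between fits none of the four. Visits every 6 or 3 months leave 24/6 − 1 = 3 or 24/3 − 1 = 7 visits in between. With an assumed independent chance q of a positive report per visit, the affected share of double-negatives is 1 − (1−q)^k. For q from 2% to 20%, that is 6% to 49% with k = 3 and 13% to 79% with k = 7. With a single interim yearly examination it is q itself. The range is too wide, and too dependent on assumption, to count as a size for this part.

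**The case against.** The strongest reply is that the planned model already contains the right contrasts. (b) vs (a) and (d) vs (c) can both be taken from the same multinomial fit, and they show no false signal. The article names no reference group and no joint test, and the choice of reported contrasts is often left to an analysis plan. The work is also described as partly exploratory, with results to be interpreted cautiously.

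Much of this stands. A reader might infer that the plan will declare a factor unrelated to course to be prognostic. The text does not say so; that follows only if the crossing coefficients are read as prognosis. But the article does fix the groups, the model class and the label of prognosis, and nothing in it rules that reading out. Cautious interpretation does not change what a coefficient estimates.

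Three other strong readings are not supported:

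- That the groups demonstrably fail to cover all patients. The lead-in ties them to two evaluations and (d) refers to both time points, so an exhaustive 2×2 reading is available. The fault is inconsistent wording.
- That interim visits go unused. The preceding descriptive mixed models of change over follow-up may use them; only the determinants step rests on two time points.
- That leaving out later years is an error. The article says "Patient follow-up is planned for a minimum period of 4 years", but it presents this analysis as a short-term, 2-year one. That is a declared choice of scope.

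**Conclusion.** The concern holds in limited form. As written, the determinants analysis does not confine prognostic claims to contrasts within baseline status, and two of every three coefficients carry prevalence at entry. That structural result needs no assumed rates. The size does: with onset and persistence equal in both levels, the crossing ratios equal the factor's baseline odds ratio (1.56, 3.50 and 2.33 in the three examples). With 450 to 550 patients, onset 15% and persistence 70%, a four-group test would flag a factor with no effect on course in roughly 43% to 54% of studies at 30% vs 40% prevalence, and more often with wider gaps. The simulation ignores centre clustering. The model is usable; what is missing is the restriction on which contrasts count as prognosis. The wording of group (a) is a separate, smaller inconsistency that should be corrected.

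**What to change.** - Reword group (a) as negative for the outcome at both baseline and 2 years.
- Keep the four groups as a descriptive table.
- Base prognostic conclusions on two conditional analyses, each with centre random effects: onset among baseline-negatives, (b) vs (a), and persistence among baseline-positives, (d) vs (c).
- State that the baseline status of the outcome itself is not used as a determinant.

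A transition model over the annual examinations is an optional extension.

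The cost is wording and programming; no new data are needed. The real price is smaller numbers per question. Under the illustrative rates in the 30% vs 40% example, 500 patients split into about 276, 49, 53 and 122 in groups (a) to (d). The onset question then has about 325 patients with 49 onsets, and the persistence question about 175 patients, of whom 53 resolve. That limits how many determinants each model can support.
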